## Intervention and Follow-up

Couples that are eligible for the study will be selected on the day of OPU based on all inclusion and exclusion criteria (as described under “D. Subject inclusion/exclusion criteria”) and will be asked to participate in the study by signing the IC. A randomization list will determine to which group the first half (or one extra in case an odd number is available) of the oocytes will be assigned. As to prevent selection bias, oocytes will be assigned to both groups under low magnification and different cumulus expansion stages will be evenly divided. Oocytes selected for ICSI will be denuded and injected on the day of OPU after which their pre-implantation development will be followed by time lapse imaging. IVF oocytes will be inseminated (individual or per two) overnight with 10.000 PR sperm cells in a G185 incubator (K systems) and denuded in the morning of day 1 after which they will be transferred to the time lapse imaging incubator. Blastocysts of sufficient quality (to determine this, morphokinetic parameters shall be measured) will be biopsied on day 5-7 after which the blastocysts are vitrified individually. PGT-A (NGS platform) is performed on all TE biopsy samples and the ploidy state and mtDNA score will be provided. All annotated time lapse imaging data will be gathered and combined with the pre-implantation data, PGT-A data (ploidy state and mtDNA copy number) and all general patient and cycle characteristics. Patients with euploid embryos available will receive a FET and implantation rates and (clinical) pregnancy outcomes will be recorded.

The follow-up of the patients does not deviate from a normal fertility trajectory.

Quantification of the determining variables:

The primary outcome variable is the ploidy state

Secondary outcome variables are the (i) embryo development defined by the number of COCs retrieved, maturation and fertilization rate, embryo development analysed on day 3 and day 5, total number of embryos used for the patient, day of biopsy and the morphokinetic parameters; (ii) mtDNA copy number and (iii) the clinical outcome.

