# Abstract

ICSI is commonly used in PGT cases to eliminate any risk of sperm DNA contamination. With the switch from cleavage stage biopsy to biopsy of the full (hatching) blastocyst, this potential risk of contamination can be neglected and could allow the use of conventional IVF in PGT cases. Especially in cases of non-male factor infertility, the use of conventional IVF can be applied as a more ‘natural’ insemination method.

A pilot study will be performed on sibling oocytes including patients with non-male factor infertility and requesting PGT-A (NGS platform). If at least 10 cumulus oocyte complexes (COCs) are obtained after oocyte retrieval, half of the oocytes will be subjected to ICSI and the other half to conventional IVF. Preimplantation development is followed by time lapse imaging and blastocysts (day 5-7) fulfilling the biopsy criteria will undergo trophectoderm biopsy to detect the ploidy state and the mtDNA copy number.

The main objective is to analyse if the use a more physiological insemination method (IVF) has a beneficial impact on the ploidy state of the blastocyst as compared to ICSI within the same patient. As the embryos will be cultured in a time lapse imaging system, annotations can be made and the differences in maturation rate, fertilization rate and embryo development between both insemination methods can be analysed as secondary outcome parameter. On top of this, the PGT-A outcome will also display the mtDNA copy number which can be compared between IVF and ICSI biopsied sibling blastocyst. Euploid blastocysts will be transferred in subsequent FET cycles and give an indication on the clinical outcome between IVF and ICSI.

Would this study enable us to undermine the dogma to perform ICSI for all PGT cycles?

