## Subject Inclusion/exclusion criteria

*Inclusion criteria*

- Sperm parameters
  - Sperm concentration before capacitation: >15*10^6^ per ml (WHO)
    - Total motility (PR+NP,%): >40 (WHO)
    - Progressive motility (PR,%):>32 (WHO)
  - Sperm concentration after capacitation: >0.6*10^6^ per ml (not WHO defined)
    - Progressive motility (PR,%):>65 (WHO)
- ≥10 COCs after oocyte retrieval
- BMI ≤30 kg/m^2^
- Female age 18 to ≤ 40 years
- All ovarian stimulation protocols
- Fresh ejaculates
- Presence or absence of sperm morphology data: as we do not have a diagnostic sperm analysis for all patients, the presence or absence of >4% normal morphology (WHO) will not be taken into account, even with known low (<4%) normal morphology
- Couples requesting PGT-A
- Arab population

*Exclusion criteria*

- If after denudation (ICSI) only 2 mature oocytes are obtained
- If all time lapse spaces are occupied
- If the volume to be added after IVF is insufficient to perform IVF on all needed oocytes
- Presence of >1 *10^6^ per ml round cells in the ejaculate
- If a couple’s previous cycle was included in the study

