## Sample Size

Considering no study has been performed analyzing the ploidy state, mtDNA content and embryo morphokinetics by PGT-A on IVF/ICSI sibling embryos, we propose a pilot study including 30 couples to assess the feasibility of the study. Moreover, the pilot study will allow us to estimate statistical parameters which enables us to calculate a sample size in a future study in which an acceptable level of power can be established.

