# Work plan

Phase I: submission of the Biomedical Research protocol and obtaining approval and, submission (and approval) by the local ethical committee

Phase II: start of the study: including the patients

- Embryologists:
  - selecting patients that are eligible for the study in consultation with the responsible physician
  - annotating in the time lapse system
  - performing biopsy and sending the samples
- Study nurse: explaining patients about the study and obtain the IC
- Responsible physician: follow-up of the patients included
- PGT-A and mtDNA copy numberanalysis

Phase III: preparing the database

- Embryologist:
  - Make the database with extraction from SIVIS
  - Double check (with 2 embryologists) all annotations
  - Check if all the data is present in the database
  - Clean the database

Phase IV: statistics

- Statistician:
  - Perform necessary tests
  - Discuss data with embryologists and responsible physician where needed

Phase V: write paper

- Embryologists and responsible physician:
  - Write manuscript
- Statistician:
  - Write part about statistics
  - Check interpretations (results and statistical outcome)
- All other parties involved:
  - Review the manuscript

|  | 2018 | | | | | | | | | | | |  |
| --- | --- | --- | --- | --- | --- | --- | --- | --- | --- | --- | --- | --- | --- |
|  | Jan | Feb | Mar | Apr | May | Jun | Jul | Aug | Sep | Oct | Nov | Dec | |
| Phase I |  |  |  |  |  |  |  |  |  |  |  |  | |
| Phase II |  |  |  |  |  |  |  |  |  |  |  |  | |
| Phase III |  |  |  |  |  |  |  |  |  |  |  |  | |
| Phase IV |  |  |  |  |  |  |  |  |  |  |  |  | |
| Phase V |  |  |  |  |  |  |  |  |  |  |  |  | |
|  |  |  |  |  |  |  |  |  |  |  |  |  | |
|  | 2019 | | | | | | | | | | | |  |
|  | Jan | Feb | Mar | Apr | May | Jun | Jul | Aug | Sep | Oct | Nov | Dec | |
| Phase I |  |  |  |  |  |  |  |  |  |  |  |  | |
| Phase II |  |  |  |  |  |  |  |  |  |  |  |  | |
| Phase III |  |  |  |  |  |  |  |  |  |  |  |  | |
| Phase IV |  |  |  |  |  |  |  |  |  |  |  |  | |
| Phase V |  |  |  |  |  |  |  |  |  |  |  |  | |

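### The list randomises only the label of an undefined first half of the oocytes, and nothing keeps the person dividing them from knowing the arm

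*Protocol*

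**What the plan says.** The comparison is made within couples. According to the Abstract, "half of the oocytes will be subjected to ICSI and the other half to conventional IVF". The eligibility criteria set the minimum to be divided: "≥10 COCs after oocyte retrieval".

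Intervention and Follow-up gives two allocation rules in consecutive sentences. The first says that "A randomization list will determine to which group the first half (or one extra in case an odd number is available) of the oocytes" are to go. The second opens with its purpose, "As to prevent selection bias", and continues: "oocytes will be assigned to both groups under low magnification and different cumulus expansion stages will be evenly divided".

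The Work plan lists what the embryologists do, including "selecting patients that are eligible for the study in consultation with the responsible physician", time-lapse annotation and biopsy. Neither holding the list nor dividing the oocytes is on that list.

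**The concern.** Randomisation protects a comparison when whoever forms the groups cannot foresee which treatment each will receive. Here the list supplies a label for one half but does not say which oocytes make up that half. A person decides that while looking at them. If that person knows the label, the two halves can differ before insemination in ways that have nothing to do with IVF or ICSI.

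The split is what makes this comparison fair. Fertilisation, blastulation and utilisation all take the oocytes assigned to the group as denominator, and the primary outcome, ploidy, is measured on blastocysts grown from those oocytes. Couple-level comparability is not at risk, since each couple contributes to both arms. The risk lies in the within-couple contrast. The study is a pilot, but its estimates are meant to "calculate a sample size in a future study in which an acceptable level of power can be established", so a distorted contrast would carry forward into the next design.

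**Working it through.** The protocol gives no error rate, power or effect size linked to allocation, so there is no figure to reproduce. The check compares the two rules and looks for safeguards elsewhere (Abstract, Study Design, eligibility criteria, Intervention and Follow-up, Sample Size, Homogeneity analysis, Work plan).

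**1. What is randomised.** Only the group that the first half joins. The term has two possible meanings:
- The first COCs in some order, such as retrieval. Order then fixes membership, which conflicts with dividing cumulus stages evenly.
- A set formed by hand to achieve that balance. A person then chooses its members.

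**2. When the label becomes known.** The text allows two sequences:
- Split first, list second. The label cannot influence the split.
- List first, split second. The label is known during the split.

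The second rule speaks of placing oocytes in both groups rather than in neutral sets. That leans towards the second sequence but does not settle it. No section states who holds the list, when it is opened, or that the person dividing the oocytes is unaware of the arm.

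**3. What the cumulus balancing achieves.** It fixes how many COCs of each stage go to each side, not which ones. As an extreme case, if all 10 COCs share one stage, every split into 5 and 5 is balanced: 10!/(5! × 5!) = 252 possible splits. With more stages present there are fewer, but choice remains wherever a stage holds at least two COCs.

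**4. Whether a biased split could be seen later.** The Homogeneity analysis compares the control variables. The explanatory variables are sperm parameters, BMI, age, AMH, smoking, race, trigger-day hormones, stimulation, trigger, abstinence, PGT-A indication, endometrial preparation and infertility type. These belong to the couple or the cycle, so they do not distinguish the two halves of one couple's oocytes at the split. Neither cumulus stage nor any other pre-insemination oocyte feature is listed.

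**5. Scale.** At 10 COCs each arm has 10/2 = 5, so one COC exchanged between arms is 1/5 = 20% of each. With n COCs per arm the share is 1/n, so it shrinks as more are retrieved.

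To turn that into an outcome, let d be the difference between the two exchanged COCs in their chance of giving a usable blastocyst. One arm's expected utilisation rate rises by d/5 and the other's falls by d/5, so the contrast for that couple shifts by 2d/5. The documents do not give d. For an assumed d of 0.1 to 0.3, the shift is 2 × 0.1/5 = 0.04 to 2 × 0.3/5 = 0.12. Over all couples it matters only so far as exchanges favour the same arm, and nothing in the documents says how often that would happen.

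**The case against.** The strongest reply is that the text does not describe an unconcealed split. It never says that the list is read first, and forming the halves before consulting it fits the wording. It does not name who divides the oocytes; the embryologist is a natural guess, not a statement. This stands, and it limits the point to what the protocol fails to prevent.

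The protocol also names selection bias as the risk and takes a real step against it. Balancing the visible feature narrows the scope for selection, and the oocytes still carry their cumulus at the split, so maturity in the protocol's own definitions is read only later. This stands too. Bias would need a further cue visible at low magnification, and the documents identify none.

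It might be said that the maturation rate would reveal a lopsided split. It is an oocyte-level measure, but it is read on day 0 for ICSI and day 1 for IVF under different definitions, so a difference could not be traced to the split.

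Lastly, this is a small feasibility study: "we propose a pilot study including 30 couples to assess the feasibility of the study". That lowers the stakes but does not excuse the order of steps, because the correction is so cheap.

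**Conclusion.** The point holds in limited form. The protocol randomises the label of an undefined half, leaves membership of the halves to judgement, and contains nothing to keep the person exercising that judgement from knowing the arm. Cumulus balancing reduces the scope for selection without concealing anything, and the listed covariates could neither reveal nor correct a biased split. The size of any bias cannot be derived. The 1-in-5 figure shows how much of an arm one COC represents at the eligibility minimum and does not estimate bias.

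A reader might infer more, and the documents do not support it:
- *That randomisation here protects nothing.* Even with the label known, it breaks any fixed link between handling order and method and randomises which arm receives the odd oocyte. If the halves are formed first, it protects fully.
- *That the operators favour IVF.* The Justification does express a hope in that direction, but the stated primary aim is neutral, and one sentence of rationale is no evidence of conduct at the bench.
- *That the ploidy comparison is shown to be biased.* What is shown is an open route to bias, nothing further.

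This is a laboratory procedure that belongs in the protocol and is not detail properly left to an analysis plan. The sponsor should correct it before enrolment, as an inexpensive improvement rather than the repair of a demonstrated failure.

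**What to change.** Replace the two allocation sentences under Intervention and Follow-up with one sequence, for example: *The COCs are first divided under low magnification into sets A and B, balanced for cumulus expansion, with any odd COC going to A. Only then is the next concealed assignment opened, which states whether A is IVF or ICSI.*

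This removes the undefined term, keeps the cumulus balancing and the near-equal split, and makes knowledge of the arm impossible while the sets are formed. The cost is a supply of sealed or electronic assignments and a fixed order of steps. It needs the same staff and no extra patients or tests.

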# Secondary Objectives/research questions

1. Pre-implantation development parameters between both insemination methods (IVF or ICSI) defined by:

- Maturation rate: number of mature oocytes obtained in each arm
  - ICSI: defined on day 0 as the number of injected oocytes/number of COCs assigned to the ICSI group
  - IVF: defined on day 1 as the number of oocytes with an extruded PB/number of inseminated oocytes
- Fertilization rate: number of zygotes with 2PN/number of oocytes assigned to the group
- Embryo quality on day 3 defined by the Istanbul consensus (Alpha Scientists, 2011)
  - The number of blastomeres and their division pattern, fragmentation, presence of compaction, vacuoles, granulation and nuclei will divide the embryos into 3 categories: good, fair or poor
  - Cell number on day 3 for all fertilized oocytes
- Embryo quality on day 5 (Gardner and Schoolcraft,1999) defined by the Istanbul consensus (Alpha Scientists, 2011)
  - The blastulation rate: number of embryos reaching at least the BL1 stage/ number of oocytes assigned to that group: defined by a 1 (yes, the embryo is blastulating) or 0 (no, the embryo is not blastulating)
  - The expansion stage of the blastocyst and the quality of the ICM and TE will divide the embryos into 3 categories
- Utilization rate: number of embryos that can be used for the patient (=number of embryos that can be biopsied)/number of oocytes assigned to the group
- Morphokinetic parameters defined by time lapse imaging starting from the time of syngamy (Basile et al., 2014)
- Morphokinetc parameters and their effect on ploidy, day of biopsy, biopsy or not and gender

1. mtDNA (de los Santos et al., 2018) per cycle and between IVF or ICSI generated embryos:

- Mitoscore value: represents the normalized mtDNA content in (an)euploid embryos and indicates the total mtDNA content in the sample

1. Cycle outcome defined by (Zegers-Hochschild et al., 2017) per cycle and also per insemination method (IVF or ICSI):

- Pregnancy (yes or no) defined by a βhCG test of > 15IU
- Biochemical pregnancy (yes or no) defined as a pregnancy in which the hCG levels start do decrease after 1 week
- Implantation rate (%) defined by the number of gestational sacs/number of embryos transferred
- Clinical pregnancy (yes or no) defined by the ultrasonographic visualization of one or more gestational sacs, including ectopic pregnancies.

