### SECONDARY outcome measures (Dependent)

PGT-A:

- mtDNA copy number (de los Santos et al., 2018):
  - Mitoscore value: represents the normalized mtDNA content in (an)euploid embryos and indicates the total mtDNA content in the sample

Pre-implantation development:

- Number of COCs retrieved
- Maturation rate: number of mature oocytes obtained in each arm
  - ICSI: defined on day 0 as the number of injected oocytes/number of COCs assigned to the ICSI group
  - IVF: defined on day 1 as the number of oocytes with an extruded PB/number of inseminated oocytes
- Fertilization rate: number of zygotes with 2PN/number of oocytes assigned to the group
- Embryo quality on day 3 defined by the Istanbul consensus (Alpha Scientists, 2011)
  - The number of blastomeres and their division pattern, fragmentation, presence of compaction, vacuoles, granulation and nuclei will divide the embryos into 3 categories: good, fair or poor
  - Cell number on day 3 for all fertilized oocytes
- Embryo quality on day 5 (Gardner and Schoolcraft,1999) defined by the Istanbul consensus (Alpha Scientists, 2011)
  - The blastulation rate: number of embryos reaching at least the BL1 stage/ number of oocytes assigned to that group: defined by a 1 (yes, the embryo is blastulating) or 0 (no, the embryo is not blastulating)
  - The expansion stage of the blastocyst and the quality of the ICM and TE will divide the embryos into 3 categories according to Istanbul consensus
- Utilization rate: number of embryos that can be used for the patient (=number of embryos that can be biopsied)/number of oocytes assigned to the group
- Day on which the biopsy is performed (day 5,6 or 7)
- Morphokinetic parameters defined by time lapse imaging starting from the time of syngamy/PN fading (Basile et al., 2014)
  - t2: the timing to two cells
  - t3: the timing to three cells
  - t4: the timing to four cells
  - t5: the timing to five cells
  - t8: the timing to eight cells
  - SC: starting to compact
  - M: the timing to morula
  - SB: starting to blastulate
  - B: reaching a BL3 according to Gardner and Schoolcraft, 1999
  - F: reaching a BL4 according to Gardner and Schoolcraft, 1999
  - cc2: t3-t2
  - s2: t4-t3
- Biopsy yes or no: indicating developmental competence or developmental arrest
- Blastocyst gender: male or female

Clinical cycle outcome:

- Pregnancy (yes or no) defined by a βhCG test of > 15IU

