- In order to evaluate morphokinetic parameters defined by time-lapse imaging starting from the time of syngamy and their effect on ploidy, biopsy day, embryo arrest and gender, first we will present a trend chart to describe the average development times of the embryos according to the treatment. Then, growth models (linear or exponential) will be performed for each embryo, to estimate a growth parameter that can be compared between IVF and ICSI treatments.

To compare IVF versus ICSI outcomes in mtDNA:

- A t-test will be used to detect differences in the Mitoscore value depending on the treatment (IVF or ICSI) if we can assume normality distribution for Mitoscore value (in other case, a Wilcoxon test will be performed). Moreover, linear regression models will be performed to analyse the treatment effect in the presence of the remaining covariates.

To compare IVF versus ICSI outcomes in cycle outcomes:

- We will build a contingency table, and then, a chi-squared test will be used in order to compare the pregnancy, biochemical pregnancy, and clinical pregnancy results between IVF versus ICSI treatments. If we found statistical differences, a logistic regression will be performed to evaluate this differences in a model taking into account rest of explanatory variables.
- To compare the implantation rate, a t-test will be used to detect differences in this rate (a Wilcoxon test will be used if we cannot assume normal distribution of data). If we found differences, linear or Poisson regressions will be performed to evaluate them in a model taking into account rest of explanatory variables.

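### Morphokinetics help judge biopsy yet are studied for their effect on it, no biopsy is read as arrest, and the announced effects on ploidy, biopsy day, arrest and sex have no described analysis

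*Protocol*

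**What the plan says.** Four parts of the protocol bear on this point.

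- **How biopsy is decided.** Intervention and Follow-up: "Blastocysts of sufficient quality (to determine this, morphokinetic parameters shall be measured) will be biopsied on day 5-7". The Abstract refers to "blastocysts (day 5-7) fulfilling the biopsy criteria will undergo trophectoderm biopsy" without listing the criteria. Ploidy is then known for biopsied embryos: "PGT-A (NGS platform) is performed on all TE biopsy samples".
- **The objective.** Secondary Objectives/research questions lists "Morphokinetc parameters and their effect on ploidy, day of biopsy, biopsy or not and gender".
- **The variable.** SECONDARY outcome measures (Dependent): "Biopsy yes or no: indicating developmental competence or developmental arrest".
- **The analysis.** Objectives assessment announces an evaluation of the parameters "starting from the time of syngamy and their effect on ploidy, biopsy day, embryo arrest and gender". It then describes two steps: "first we will present a trend chart to describe the average development times of the embryos according to the treatment", followed by a growth model for each embryo "to estimate a growth parameter that can be compared between IVF and ICSI treatments".

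**The concern.** There are three linked problems.

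1. A measurement used to reach a decision is studied as a predictor of that decision. Whatever part of the association comes from the decision rule says how the laboratory selects embryos. It says nothing about embryo development.
2. One variable is given two meanings. Not being biopsied can follow from arrest or from a blastocyst failing the quality criteria, but the protocol names only the first.
3. The analysis section poses one question and describes the analysis of another. An IVF-versus-ICSI comparison of growth does not show whether timing is related to ploidy, biopsy day, arrest or sex.

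At stake is a secondary objective. It could yield an association with biopsy that is mistaken for biology, an arrest outcome containing embryos that did not arrest, and no planned estimate for the link to ploidy.

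**Working it through.** The protocol gives no figure on this point to reproduce: no biopsy threshold, no weight for the timings and no power calculation. The check is therefore mainly a comparison of the texts, followed by an illustration.

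**Step 1: biopsy as decision and as outcome.** Intervention and Follow-up has morphokinetic parameters measured in order to judge quality, and quality determines biopsy. Secondary Objectives/research questions then takes biopsy as something those parameters affect. On the plain reading the two overlap. Neither section says which parameters count or how heavily.

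**Step 2: biopsy and arrest.** The variable list reads no biopsy as arrest. Objectives assessment repeats the list of effects with embryo arrest standing where the objective had biopsy or not. The protocol's own rates show that these differ. Blastulation is coded 1 from stage BL1 onwards, while utilization counts only embryos suitable for biopsy. A blastocyst that misses the criteria scores 1 for blastulation, does not count towards utilization, and is read as arrested.

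**Step 3: announced effects against described analysis.**

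| Announced effect of morphokinetics on | Outcome or grouping factor in the trend chart? | In the growth-parameter comparison? |
|---|---|---|
| Ploidy | No | No |
| Biopsy day | No | No |
| Arrest | No | No |
| Sex | No | No |

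Insemination method is the only grouping factor in either step.

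**Step 4: how far no biopsy can depart from arrest (assumed inputs).** Let *a* be the share of embryos that arrest and *p* the share of the others that pass the quality criteria. The share of unbiopsied embryos that did not arrest is

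(1 − a)(1 − p) / [a + (1 − a)(1 − p)].

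With a = 0.40 and p = 0.70, neither taken from the protocol: 0.60 × 0.30 = 0.18, and 0.18 / (0.40 + 0.18) = 0.31. If every non-arrested embryo passed (p = 1), the share would be 0.

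**Step 5: association created by the decision rule (assumed inputs).** The inputs were:

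- 150 embryos and 2000 runs. For scale, 30 couples × at least 10 oocyte complexes = 300, or 150 per method; these are oocytes, so 150 embryos is an assumption.
- A standard normal timing score M, independent of arrest, with a and p as in step 4.
- Quality = w·M + √(1 − w²)·e, with e standard normal. An embryo is biopsied if it has not arrested and its quality exceeds the cut-off that 70% pass.
- A two-sample t-test of M by biopsy status at the 5% level, ignoring clustering by couple.

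| Weight w of timing in the decision | Runs with a significant association |
|---|---|
| 0 | 4% |
| 0.3 | 32% |
| 0.5 | 74% |
| 0.7 | 97% |

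With no weight the test keeps its nominal level. Any excess comes from the decision rule alone.

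**Step 6: ploidy seen only after selection (assumed inputs).** Take a true correlation of 0.30 between timing and ploidy liability, with half the embryos biopsied. The correlation among biopsied embryos is then 0.30 at w = 0, 0.28 at 0.5, 0.25 at 0.7 and 0.19 at 1.0. A ploidy model therefore describes embryos selected for biopsy and should say so.

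**The case against.** **The circularity may be small.** The protocol says that parameters are measured to judge quality, not that early cleavage timings decide biopsy. Day 5 quality is graded on expansion, inner cell mass and trophectoderm. The morphokinetic list includes the times of reaching BL3 and BL4, so the remark may mean stage reached. This stands. A reader might infer that an association will be found by construction, but the text does not support that: the weight is unknown, and at zero weight there is no inflation.

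**Arrest is worded as a proxy.** The variable is said only to indicate arrest, and blastulation and stage times are recorded separately. A reader might infer that every unbiopsied blastocyst is misclassified. That goes too far, because an embryo that starts to blastulate and never progresses may well have arrested. What remains is that the stated reading cannot tell the two groups apart, although the collected data could.

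**The model may be in a separate analysis plan.** This is fair, and the protocol also says that time-lapse and PGT-A data will be combined. The supportable claim is that these effects are announced without an analysis that addresses them, not that they will go unanswered. It remains a protocol finding because the section names the question and then describes an analysis that answers a different one.

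**The growth fits.** Arrested embryos lack late stages, and a reader might infer that the growth comparison is biased. No bias has been shown. Limiting the fits to stages that all embryos reached could itself condition on survival.

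**Conclusion.** The point holds in a limited form.

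- The association between morphokinetics and biopsy is partly built in to the extent that timings enter the decision. It should not be read as a developmental effect.
- No biopsy and arrest are different variables that the protocol treats as one.
- Neither described step addresses the announced effects on ploidy, biopsy day, arrest and sex.

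The second and third conclusions rest on the text alone and hold even if timing has no weight in the decision. The first rests on the plain reading of Intervention and Follow-up.

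The true size cannot be derived from the protocol. The figures of 4% to 97% and 31% illustrate the mechanism under assumed inputs and are not estimates for this trial. The issue concerns a secondary objective in a pilot of 30 couples and leaves the planned primary IVF-versus-ICSI comparison of ploidy unchanged. It should be settled before analysis.

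**What to change.** The clinical biopsy rule need not change. The protocol should state whether morphokinetic parameters enter that decision and, if so, which ones. Then:

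1. **Separate the variables.** Keep biopsy yes/no and arrest apart. Define arrest in advance from time-lapse annotation as no further stage progression by the end of culture. Code non-arrested, unbiopsied blastocysts as their own category. Defining arrest as failure to start blastulating would not do, since an embryo that stalls after that stage would count as not arrested.
2. **Report morphokinetics against biopsy yes/no descriptively**, without a test read as a developmental effect.
3. **Add embryo-level models** with a random effect for couple and insemination method as covariate. Model ploidy, sex and biopsy day (as an ordinal outcome) in biopsied embryos only, and say so. Model arrest separately.
4. **Use a non-redundant set of early timings**: either t2, t3, t4, t5 and t8, or t2 with cc2, s2 and the later timings. The protocol defines cc2 = t3 − t2 and s2 = t4 − t3, so entering both sets makes the predictors exactly collinear.

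The growth-parameter comparison can stay as planned.

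The cost is some rewording and a little more analysis, since the annotations are already to be collected. There are two limits to state. The ploidy, sex and biopsy-day results apply only to embryos selected for biopsy. An embryo that arrests before a given timing has no value for it, so the arrest model covers embryos that reached the last timing entered.
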